### Interventions

1.4

#### Control group

1.4.1

This group will just perform the breath stacking technique. For this, the patients will have a choice between using an inflated oronasal mask (Lumiar Health Care, Sao Paulo, Brazil) or a mouthpiece (Respironics, Utah, USA). The caregivers of the patients will be trained by the research-coordinators ([name]) to perform the technique at least two sessions per day, one in the morning and one at bedtime. The caregivers will be monitored continuedly, with monthly visits to the referral center to ensure that the technique is performed well. All research coordinators have experience with the techniques and worked with respiratory management in ALS patients for at least 3 years.

To performed the breath stacking technique, we utilize the protocol previously described by Bach et al. [5]. The lungs are inflated as fully as possible by stacking successive breaths without expiration until the patients’ lung insufflation capacity (LIC). The participant will be instructed to sustain the air in the lung, closing the glottis. Once the lungs are maximally inflated, the compressed air volume is released under expiratory muscle force, thus generating a cough with lung and chest wall recoil. They will perform 5–8 cycles of breath stacking per session, stacking 3–5 breaths per cycle.

#### Experimental group

1.4.2

This group will perform the breath stacking technique in addiction with EMT. The valve will be changed to the one-way valve called VUP (Lumiar, Sao Paulo, Brazil), a one-way valve (Fig. 2) that allows patients blow out air with a counter resistance during all expiratory phase.

**Fig. 2 fig2:**
[figure not shown]
VUP valve used in EMT program.

. The initial expiratory pressure will be 8 cmH_2_O and can be changed at each visit depending on participants’ tolerance, whether it is easy or difficult to exhale assessed by research coordinators. The participants will be encouraged to blow out as slowly that they can. Both protocols will be performed for 24 weeks, and outcome measurements will be performed every 8 weeks.

#### Safety and adverse events reporting

1.4.3

A serious adverse event is defined in this study as any event occurring either during or up to 60 min following the trial intervention or outcome assessment that is life threatening or results in death, hospitalization or prolongation of existing hospitalization, disability or incapacity. Minor adverse events directly relating to intervention or outcome measure sessions can include: aerophagia, severe breathlessness, new or progressive pain, altered mental status, palpitations and progressive fatigue [4]. Following each intervention and outcome measure session trial staff are required to complete data entry forms indicating if a serious or minor adverse event has occurred. In the case of serious adverse events the study chief investigator is notified immediately, participants are managed appropriately, and the incident will be reported to the relevant hospital ethics committee.

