## Conclusion

3

ALS patients have a poor survival and demonstrate high burden of disease when their bulbar and respiratory function decline. This randomized trial will assess the effects of home-based program in pulmonary and bulbar function. If beneficial, the intervention is designed in way to enable easy translation into practical guidelines for this population.

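### The serious adverse event definition ends 60 minutes after a session or assessment, so serious events that begin later are never reportable as SAEs

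*Protocol article*

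**What the plan says.** Section 1.4.3 (Safety and adverse events reporting) defines an SAE as "any event occurring either during or up to 60 min following the trial intervention or outcome assessment that is life threatening" or one that "results in death, hospitalization or prolongation of existing hospitalization, disability or incapacity". Events that meet this definition go to the chief investigator at once and are reported to the hospital ethics committee. Minor adverse events are a separate category, tied to the sessions themselves. On recording, the section states: "Following each intervention and outcome measure session trial staff are required to complete data entry forms", to show whether a serious or minor event has occurred.

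The sessions are described elsewhere. Under section 1.4.1 (Control group), caregivers are trained "to perform the technique at least two sessions per day, one in the morning and one at bedtime", and "The caregivers will be monitored continuedly, with monthly visits to the referral center"; the stated purpose of that monitoring is good technique. Section 1.4.2 (Experimental group) adds: "Both protocols will be performed for 24 weeks, and outcome measurements will be performed every 8 weeks". The Conclusion calls the intervention a home-based programme.

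Outside the SAE rule, section 1.4.4 (Outcomes) has FVC, SVC, MIP, MEP and PCF measured at baseline and weeks 8, 16 and 24, and survival collected at 2 years. Section 1.6 plans Kaplan-Meier curves and Cox regression for survival.

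**The concern.** Seriousness normally decides whether an event is an SAE, and timing relative to treatment helps to judge relatedness. Here timing is built into the definition. A respiratory admission three hours after a session meets the hospitalisation criterion but is not an SAE, so neither the immediate notification nor the ethics report applies. The minor-event category is not designed to catch it either.

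This matters in this population. The Introduction says that ALS leads to chronic respiratory failure and that impaired cough is a leading reason for admission. The experimental arm adds expiratory resistance over 24 weeks, and section 1.4.3 itself names progressive fatigue as a possible adverse event, so harm that builds up over time is foreseeable. A 60-minute window is suited to acute harm only.

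A second, smaller problem is practical. Staff are to complete a form after each session, but caregivers deliver the sessions at home and centre visits are monthly. The article does not say how an event at home reaches the form.

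**Working it through.** The plan gives no expected SAE count or capture rate, so there is no figure to reproduce. The check is how much follow-up time the definition covers.

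**Which events the limit governs.** The time restriction comes before the whole list of criteria, so it applies to death, life-threatening events, hospitalisation and disability alike. Reading the trial intervention as the entire 24-week course would remove the problem, but a 60-minute tail on a 24-week course makes little sense, and the same section goes on to speak of individual sessions.

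**Inputs**
- Sessions per day: at least 2 (section 1.4.1). The experimental arm is assumed to follow the same frequency. Four is shown as a higher case.
- Window: the session plus 60 minutes (section 1.4.3).
- Session length: not given in minutes; 5 to 30 minutes assumed.
- Duration: 24 weeks (section 1.4.2).

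**Share of the day inside the window**, w = sessions × (60 + session length) / 1440, with windows that do not overlap:

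| Sessions per day | Session length | Inside | Outside |
|---|---|---|---|
| 2 | 5 min | 130/1440 = 9.0% | 91.0% |
| 2 | 30 min | 180/1440 = 12.5% | 87.5% |
| 4 | 5 min | 260/1440 = 18.1% | 81.9% |
| 4 | 30 min | 360/1440 = 25.0% | 75.0% |

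The three outcome assessments after randomisation add almost nothing: 3 × 60 minutes is 3 hours out of 24 × 7 × 24 = 4032 hours, or 0.07%, ignoring the length of the assessment.

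**If events are not evenly spread.** If the hourly rate inside the window is RR times the rate outside, the share captured is w·RR / (w·RR + 1 − w). Half of the events are captured when RR = (1 − w)/w:
- two sessions of 30 minutes: 1260/180 = 7.0
- two sessions of 5 minutes: 1310/130 = 10.1
- four sessions: 1080/360 = 3.0 to 1180/260 = 4.5

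At two sessions a day, then, the rate within the window would have to be about 7 to 10 times the rate outside it for half of the serious events to qualify.

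**Recording route.** The minimum is 2 × 7 × 24 = 336 sessions per participant. Against this stand about 6 monthly visits and 3 outcome appointments after randomisation, so about 9 contacts at most, and fewer if they coincide. Staff therefore cannot be assumed to be present at most sessions after which a form is due.

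**The case against.** The strongest reply has four parts.

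**Respiratory harm is measured anyway.** A reader might infer that the trial could not detect expiratory loading that hastens respiratory failure. The document does not support that. FVC, SVC, MIP, MEP and PCF are compared between arms, time from diagnosis to prescription of non-invasive ventilation is recorded, and 2-year survival is analysed. Intensive care admission must also be noticed, because section 1.2 lists it as an exclusion. This part stands and narrows the loss. None of these sources, however, records ordinary hospitalisation, disability or life-threatening events as safety data, and none brings prompt reporting.

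**Even timing is an assumption.** The document gives no event times. Acute harm from a session could cluster inside the window, and many events outside it would be ordinary disease progression. The percentages are therefore not the share of intervention harm that is missed. This stands.

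**The staff form need not conflict with home delivery.** Forms could be filled in from caregiver reports, and a condensed article may leave that route to the full protocol. This also stands: the passages are hard to reconcile but not shown to be incompatible. Staff logging is a recording step, not part of the SAE definition.

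**Fatigue and breathlessness are listed as minor events with no 60-minute limit.** True, but that category is confined to events tied directly to sessions and does not trigger SAE reporting.

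None of this rescues the definition itself, which is a stated rule and not an omitted detail.

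**Conclusion.** The point holds in a limited form. As written, a serious event that starts more than 60 minutes after a session or assessment is not an SAE and does not enter SAE recording, notification or ethics reporting. What is lost is mainly non-fatal serious events, above all hospitalisation outside intensive care and disability, together with prompt reporting of deaths that would otherwise surface only in the survival follow-up.

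The size depends on even timing of events, sessions of 5 to 30 minutes, and two to four sessions a day actually performed. On those terms 75 to 91% of serious events would fall outside the window. A reader might go further and conclude that most serious harm from the intervention would be missed, or that the trial would report almost no SAEs. Both are inferences that the document does not establish, because it gives neither event timing nor event rates. Allocation and the analysis of the primary outcomes are not affected.

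**What to change.** - Define an SAE by seriousness alone, from randomisation to the 24-week visit, whatever the time since the last session.
- Record relatedness to the intervention as a separate item, and keep occurrence within 60 minutes as a descriptive flag.
- Ask patient and caregiver about serious events at each existing monthly and outcome visit, and tabulate the events by arm.
- Reconcile the staff-completed form in section 1.4.3 with the caregiver-delivered home sessions in section 1.4.1 and the Conclusion, stating how events at home reach staff.

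The cost is a protocol amendment and more reporting, since disease-related admissions will now count; they can be listed by arm as expected events. No new visits are needed. Recruitment began in August 2019 and is ongoing, so participants already enrolled need their earlier events ascertained retrospectively, or flagged as collected under the narrower definition.

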## Introduction

1

Amyotrophic lateral sclerosis (ALS) is a progressive neurodegenerative disease affecting both upper and lower motor neurons, which leads to a loss of voluntary muscle control [1]. As the disease progresses, muscles of respiration are affected, leading to chronic respiratory failure [2]. Respiratory failure is primarily due to respiratory muscle weakness, leading ALS patients to cough impairment, one of the main causes of hospitalization [3,4]. Producing an effective cough initially requires taking a deep breath with the inspiratory muscles, followed by maximum contraction of the expiratory muscles, with glottis closure and subsequent opening using the oropharyngeal muscles, generating an expiratory flow due to contraction of expiratory muscles capable of eliminating secretions [5,6]. This represents the inspiratory, compression and expiratory phases of cough production. Thus, strategies to enhance effective cough and lung recruitment should be recommended in ALS patients [7].

Among these strategies suggested for respiratory management in ALS patients, breath stacking has been used to assist cough in neuromuscular disorders [8]. The breath-stacking technique uses a manual resuscitation bag with one-way valve to deliver large breath volumes to the patient via a suitable interface [9]. Periodic lung expansion by breath stacking decreases basal atelectasis, and maintains compliance of the lungs and chest wall, with increases of Peak cough flow (PCF) and cough effectiveness [5]. Rafiq et al. have demonstrated that breath stacking should be recommended as a first line intervention for lung recruitment and cough augmentation in ALS patients, with no differences between breath stacking and mechanical insufflator-exsufflator for survival, quality of life and hospitalization [9].

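### Section 1.4.3 names severe breathlessness and altered mental status as minor events without reconciling that list with the serious-event definition, and admits minor events only after a relatedness judgement by staff not stated to be blinded

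*Protocol article*

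**What the plan says.** Section 1.4.3 of the protocol article defines a serious adverse event by timing and outcome. On timing, it covers "any event occurring either during or up to 60 min following the trial intervention or outcome assessment", and no relatedness condition is attached. To count as serious, such an event must also meet one of the outcome criteria, which read: "life threatening or results in death, hospitalization or prolongation of existing hospitalization, disability or incapacity".

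Minor events are introduced differently: "Minor adverse events directly relating to intervention or outcome measure sessions can include: aerophagia, severe breathlessness, new or progressive pain, altered mental status, palpitations". Progressive fatigue closes the list.

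After each session, "trial staff are required to complete data entry forms indicating if a serious or minor adverse event has occurred". Onward reporting is described for one class only: "In the case of serious adverse events the study chief investigator is notified immediately", with a report to the ethics committee. No route is given for minor events.

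Three other places bear on how the rule works:

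- Section 1.4.1 has caregivers trained "to perform the technique at least two sessions per day, one in the morning and one at bedtime", with monthly visits to the centre.
- Section 1.4.2 says the expiratory pressure in the experimental arm "can be changed at each visit depending on participants’ tolerance, whether it is easy or difficult to exhale assessed by research coordinators".
- Section 1.4.4 states that the research assistant who assesses outcomes is blinded. No blinding is stated for the staff who complete the event forms.

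**The concern.** There are two separate faults in the stated rule.

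**Classification.** One class is defined by what happens to the patient, the other by examples of symptoms. The two can overlap: an episode of altered mental status could be read as incapacity, which is a seriousness criterion, or as a listed minor event. The article does not say which reading prevails, yet only one of them leads to a report. The form asks staff to choose between serious and minor, and the protocol's own list steers them to minor.

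**Relatedness as a condition of entry.** A minor event counts only if it is directly related to a session, and no criteria are given for that judgement. The Introduction says of this population: "As the disease progresses, muscles of respiration are affected, leading to chronic respiratory failure". It is a reasonable clinical inference, though not stated in the article, that breathlessness and fatigue will also arise from the disease. Staff must then decide between session and disease before anything is written down, and an event not recorded at that point cannot be recovered at analysis.

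At stake is the tolerability evidence on the new valve. The article's Conclusion intends the home programme to pass easily into practical guidelines, so a reader will want a harm record that does not depend on what staff believe about the valve.

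**Working it through.** No figure in the plan needs to be reproduced. The check sets the stated rules side by side.

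| Feature | Serious event | Minor event |
|---|---|---|
| Basis of definition | Outcome | Symptom examples |
| Time limit | During, or within 60 min after, an intervention or assessment | Tied to a session, no time limit given |
| Relatedness needed | No | Yes, directly related |
| Stated reporting route | Chief investigator at once, then ethics committee | None |

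**Step 1: the overlap.** Take an episode of severe breathlessness or altered mental status.

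- If it meets a seriousness criterion within the window, it fits the serious definition and is notified.
- If it meets none, it falls under the minor list. It is entered on a form if judged related, and goes no further under the stated text.
- If it is arguable whether a criterion is met (incapacity is the obvious case), the text gives no rule of precedence.

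**Step 2: who judges cause.** The form is completed by trial staff. The research coordinators set the valve pressure in the experimental arm, so they know the arm. The outcome assessor is blinded, but the article does not say whether that person ever completes the form. It is therefore established only that the staff making the judgement are not stated to be blinded.

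**Step 3: when the judgement is made.** At the stated minimum, each participant has 2 × 7 × 24 = 336 sessions over 24 weeks. Between monthly visits there are about 2 × 30 = 60. Caregivers deliver these, whereas the form is for trial staff after each session. If staff learn of events only at visits (an assumption, since the article does not say), relatedness is judged in retrospect across some 60 sessions.

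**Step 4: effect on a count by arm.** Let p be the true proportion of patients with such a symptom in an arm, and a the proportion of those that staff attribute to a session. Assume every episode comes to notice. Then

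recorded proportion = p × a

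recorded ratio between arms = (p_EMT / p_control) × (a_EMT / a_control)

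The recorded ratio equals the true ratio only if a is the same in both arms. Even then, with a below 1, the recorded difference is the true difference multiplied by a. The documents give no value for p or a, so neither size nor direction can be stated. If staff suspect the resistance, a_EMT is raised; if they trust it, a_EMT is lowered.

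**The case against.** The strongest reply has four parts.

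**The list is illustrative.** It says what minor events can include, and the form lets the same symptom be entered as serious or minor. Severity and seriousness are also different concepts, so a severe but non-serious event is no contradiction. This stands. A reader might infer that possible respiratory failure triggers no notification. The text does not support that: the serious definition takes in any event in its window and needs no attribution, so respiratory failure that is life threatening or leads to hospitalization in that window is serious and is notified at once. What survives is the absence of a rule for overlap and of a route for episodes that meet no criterion.

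**No arm comparison of harms is stated.** This also stands. Harms are not among the listed outcomes, and section 1.6 names no adverse event analysis. A reader might infer that a biased safety comparison is planned, but the article does not say so, and any such analysis may sit in a document not shown. The point is conditional: if non-serious harms are summarised by arm, the counts carry the attribution filter.

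**A condensed article leaves form detail elsewhere.** That is fair for wording of questions and grading scales. It does not answer a stated restriction on which minor events count, or two definitions that are stated and not reconciled.

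**Safeguards exist.** Caregivers are monitored with monthly visits, and a change of resistance by tolerance may lower the load as well as raise it. Both are true, and the pressure adjustment is no hazard in itself. Neither removes the relatedness condition.

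**Conclusion.** The point holds in a bounded form. Section 1.4.3 leaves two potentially grave symptoms in a minor list that is not reconciled with the serious definition, and gives no reporting route when they meet no seriousness criterion. It also makes a causal judgement, by staff not stated to be blinded, a condition for a minor event to count. Serious events are outside this second fault.

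No numerical size can be given without invented event and attribution rates. The conclusion assumes that staff apply the wording as written, and that breathlessness and fatigue in these patients can arise from ALS as well as from a session. It is a change that should be made. It does not touch the efficacy outcomes.

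**What to change.** In section 1.4.3:

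- **Recording.** Ask the same symptom questions in both arms and record every new or worsened event, regardless of relatedness. Make relatedness and severity separate fields on the form. If harms are summarised, report all-cause events by arm, with attributed events as a secondary display.
- **Classification.** Reconcile the minor list with the outcome-based serious definition, say which governs when both apply, and state the reporting route for severe breathlessness and altered mental status. The clinical threshold and the response are for the sponsor to set.

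The cost is one revised form and one protocol paragraph. The downside is more recorded events, many of them due to ALS, in a trial of 42 participants. The article describes recruitment as ongoing, so the change should come soon and its date should be noted, because events before it will have been collected under the narrower rule.

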#### Outcomes

1.4.4

Outcomes will be assessed during individual appointments at baseline, 8 weeks, 16 weeks and 24 weeks by a research assistant blinded to group allocation. At baseline, demographic and clinical details will be recorded, including age, sex, location of onset of symptoms, time of diagnosis, treatment details and social history. Survival data will be collected after 2 years post study recruitment.

Treatment efficacy will be determined by changes in decline rate of the primary outcomes (Maximal Inspiratory Pressure [MIP], Maximal Expiratory Pressure [MEP], Peak Cough Flow [PCF], Forced Vital Capacity [FVC) and Slow Vital Capacity [SVC]) from baseline to 24 weeks.

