**Methods:**

This parallel-group, assessor-blinded randomized controlled trial, powered for superiority, aims to assess pulmonary function, respiratory muscle strength, peak cough flow as primary outcomes. Forty-two participants are being recruited referral neuromuscular disease center at Brasilia, Brazil. Following baseline testing, participants are randomized using concealed allocation, to receive either: a) breath stacking technique alone or b) breath stacking technique plus EMT.

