Expiratory muscle training (EMT) has been investigated as a new effective tool to enhance maximal PCF in individuals with neuromuscular diseases. This technique aims to improve subglottic air pressure generation, swallowing and airway clearance [10]. Reyes et al. have shown that EMT plus breath stacking improved voluntary and reflex cough in Parkinson disease [11]. Plowman et al. have demonstrated that 5-week EMT training was feasible and led to improvements in respiratory and bulbar function in ALS patients [10,12]. However, both studies have not used the techniques together, which may improve the clinical results. Of note, the randomized controlled trials performed in ALS patients have not investigated the addiction of EMT together breath stacking in this population.

This trial aims to determine if breath stacking plus EMT is more effective than breath stacking alone to decrease the decline rate on the inspiratory/expiratory muscle strength, pulmonary function testing and voluntary PCF in ALS patients. We hypothesize that those receiving breath stacking plus EMT will have a slower decline in these parameters from baseline to 6 months, compared to patients that receiving breath stacking alone. The key secondary outcomes are to assess whether EMT plus breath stacking is superior to breath stacking alone to swallowing function and ability to speech. This protocol is reported according to the Standard Protocol Items: Recommendations for interventional Trials (SPIRIT guidance) [13].

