##### Pulmonary function and respiratory muscle strength

1.4.4.1

The PFTs will be measured using a Vitalograph 6800 PFT spirometer (Vitalograph Inc, USA) and the decision whether to use the mouthpiece with nasal clip or the mask will be based on the evaluation of each single patient, specifically on the presence of facial muscle weakness. The PFTs that will be included are the FVC and SVC, which will be performed in both and supine positions; they are expressed both as absolute value, in FVC% and SVC%, respectively) [14]. The patient is guided to inhale deeply and, subsequently, to expire as fast as far they could.

Maximal inspiratory (MIP), and maximal expiratory pressure (MEP) were measured as previously described by Black & Hyatt [15]. Sniff nasal inspiratory pressure (SNIP) will be measured at functional residual capacity as previously described [16]. The highest value from three or more attempts will be selected for analyses and standardized to predicted percentages of Brazilian population [17].

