### Sample size calculation

1.5

This study is powered to detect a clinical meaningful difference in decline rate of pulmonary function (% predicted FVC). Based on meta-analysis conducted by Silva et al. [21], the minimal clinical important difference (MCID) from baseline to 1 year is 2–6%, 16 participants for each arm will need to be recruited with 80% power at two-tailed 5% level of significance. After take into account 30% attrition, a total sample size of 42 participants is required.

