### Statistical analysis

1.6

Baseline characteristics will be summarized, including age, sex, time of diagnosis, onset of symptoms local, drugs, primary and secondary outcomes, and imbalances will be investigated.

For each variable, the Shapiro Wilk test will be used to evaluate the normality of the distribution and the Levene test will be performed to evaluate the homogeneity of variance. The differences between groups will be analyzed by the unpaired *t*-test and for continuous variables and chi-square test for categorical variables. The decline rate will be calculated as the difference between baseline and final observation, dividing the result by the number of months between baseline and last evaluation. Spearman test will be used to evaluate the longitudinal decline correlations between pulmonary function tests and both bulbar impairment and disease progression rate.

Exploratory analysis of 2-year survival will include descriptive Kaplan-Mayer survival curves and cox regression with treatment intent.

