## Discussion

2

This study will assess the impact of expiratory muscle training associated with breath stacking technique on pulmonary function, respiratory muscle strength, peak cough flow and functional assessment in ALS patients. We chose the pulmonary function parameters and cough efficacy as primary outcomes because they plays a critical role in predicting the prognosis of these patients, both in terms of survival and functional ability [22].

A recent study suggests that expiratory muscle training was feasible and well-tolerated in ALS patients, and led to improvements of expiratory muscle strength and swallowing kinematics [10]. However, no differences were noted for FVC. The breath stacking technique can increase inspired volumes that lead to greater peak cough flow, allowing for improvements in mucus clearance and reduction in atelectasis (6). We believe that the increase of inspired volume may increase the efficacy of expiratory muscle training in the ALS population.

The American Academy of Neurology, Practice Parameters has recommended that breath stacking technique as a respiratory aid in patients with neuromuscular diseases. This trial aims to determine the impact of an inspiratory and expiratory synergist program in ALS patients using the same resuscitation bag with an addiction of a new valve (VUP) that allows for increased lung capacity and the addiction of a submaximal load to expiratory muscles during the expiration phase, which may provide muscular conditioning in ALS patients and contribute to a maintained bulbar function.

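### Efficacy rests on five unranked primary outcomes, but power and the 5% level are set for % predicted FVC alone, and no success rule links the two

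*Protocol article*

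**What the plan says.** Outcomes (1.4.4) states that "Treatment efficacy will be determined by changes in decline rate of the primary outcomes", and names these as MIP, MEP, PCF, FVC and SVC, measured from baseline to 24 weeks. That makes five primary outcomes, and none is marked as leading.

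Other sections also use the plural. The Methods paragraph of the abstract says the trial "aims to assess pulmonary function, respiratory muscle strength, peak cough flow as primary outcomes". The Discussion says "We chose the pulmonary function parameters and cough efficacy as primary outcomes". The hypothesis in the Introduction is that the experimental group "will have a slower decline in these parameters from baseline to 6 months", which does not say whether every parameter or any one of them is meant.

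Sample size calculation (1.5) is about a single outcome: "This study is powered to detect a clinical meaningful difference in decline rate of pulmonary function (% predicted FVC"). It gives 16 per arm, 80% power and a two-tailed 5% level, then 42 in total after 30% attrition. The 5% is not divided.

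Statistical analysis (1.6) assigns one test to continuous variables: "The differences between groups will be analyzed by the unpaired" t-test. It gives no order of testing and no joint criterion.

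Section 1.4.4.1 adds that the tests include "the FVC and SVC, which will be performed in both and supine positions" and that they are expressed as absolute and percent values.

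**The concern.** Section 1.4.4 says what decides efficacy, and section 1.5 says what the trial is sized to decide. They describe different decisions. Five co-equal outcomes can be combined in at least two ways: success on any one, or success on all. The choice determines both the false positive rate and the power, and the article does not make it.

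The superiority claim is at stake. If the rule stays open until results are seen, a single significant result out of five could be presented as a positive trial at the 5% level when the real error rate is higher. Four non-significant results beside a significant FVC could equally be argued to be a failure.

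**Working it through.** **Inputs from the article.** Five primary outcomes (1.4.4); one sized outcome, % predicted FVC, with two-sided alpha 0.05, 80% power and 16 per arm (1.5); unpaired t-test (1.6).

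**Assumed, because the article gives no figure.** The correlation between outcomes is taken as equal across pairs and varied from 0 to 0.9.

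**1. The plan's own figure.** The 16 per arm cannot be rebuilt, because section 1.5 gives no standard deviation and states the effect as a range (2–6%). It can be inverted to find the standardized effect that it implies:

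- Normal approximation: d = (1.960 + 0.842) × √(2/16) = 2.802 × 0.3536 = 0.99.
- Using the t-test: d = 1.02.

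These figures hold for one outcome tested at 0.05. The total of 42 follows from 32 × 1.30 = 41.6.

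**2. If any one of five suffices.** With no true effect on any outcome and independent tests, the chance of at least one two-sided p<0.05 is 1 − 0.95^5 = 22.6%. For equally correlated normal statistics, the chance is 1 − P(all five |Z| < 1.96), by numerical integration. Counting only significant results in favour of the experimental arm, the independent case is 1 − 0.975^5 = 11.9%, to be compared with 2.5% for one test.

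| Assumed correlation | Any of 5, either direction | Any of 5, favouring experimental arm |
|---|---|---|
| 0 | 22.6% | 11.9% |
| 0.3 | 20.9% | 10.5% |
| 0.5 | 18.3% | 9.2% |
| 0.7 | 14.8% | 7.4% |
| 0.8 | 12.7% | 6.4% |
| 0.9 | 10.2% | 5.1% |

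Simulated unpaired t-tests at 16 per arm agree: 22.7%, 18.5% and 15.2% at correlations 0, 0.5 and 0.7. FVC and SVC are probably much closer to each other than to the rest. With that pair at 0.9 and all other pairs at 0.3 to 0.5, the simulated rate is 17–19%.

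**3. If all five must succeed.** The false positive rate is at most 5%, since the joint event cannot be more likely than one test succeeding. Suppose each outcome has 80% power, which the article does not claim for any outcome but FVC. Joint power is then 0.80^5 = 33% if the outcomes are independent. By the same integration it is 51% at correlation 0.5 and 69% at 0.9. It reaches 80% only if the outcomes are perfectly correlated.

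**4. Price of keeping five primaries.** The strictest Holm step tests at 0.05/5 = 0.01. At 16 per arm and the implied effect, power per outcome at that step is:

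- Normal approximation, d = 0.99: Φ(0.99 × √8 − 2.576) = Φ(0.226) = 59%.
- t-test, d = 1.02: 56%.

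About 24 evaluable participants per arm would be needed for 80% at 0.01.

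**The case against.** **The any-one rule is not in the document.** A reader might infer that any of the five p-values supports the claim, so that the trial's false positive rate simply is 15–23%. The article does not support this. Section 1.4.4 refers to the primary outcomes in the plural, and the hypothesis can be read as requiring all of them. This objection stands, so every error rate here is conditional on the rule. It does not rescue the plan, because the all-required reading breaks the stated power instead.

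**The rate depends on unknown correlations and on direction.** This also stands. Independence is an upper bound, since two of the five are vital capacities from the same spirometer. For that reason the range runs down to correlation 0.9, and the favourable-direction rates are shown. At 0.9 the rate is still twice the nominal level.

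**Positions and scales could multiply the tests.** A reader might count two positions for FVC and SVC as seven primary tests, or add absolute and percent scales to reach eleven, and arrive at 1 − 0.95^7 = 30% or 1 − 0.95^11 = 43%. These figures should not be used. Section 1.4.4.1 describes how FVC and SVC are measured and expressed; it does not make each version a primary test. Section 1.5 already fixes the scale for FVC. Treating versions of one vital capacity as independent is also implausible. What remains is narrower: the position for FVC, and the position and scale for SVC, are not fixed.

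**Multiplicity is often left to an analysis plan.** An analysis plan that is not shown here may contain an adjustment, and its absence from a journal article is no fault. But the article itself fixes which outcomes are primary and what the trial is powered for, and these conflict. An analysis plan could not reconcile them without changing either the primary-outcome definition or the power statement.

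**Conclusion.** The concern holds as a conflict between two stated rules: five unranked outcomes decide efficacy, while size, power and alpha belong to one, with no success criterion between them.

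If any one outcome suffices, the two-sided familywise error is about 10–23%, and about 15–21% at correlations of 0.7 to 0.3. If all five are required, the error is controlled but power falls below the stated 80%. The correlations, and in the all-required case 80% power for each outcome, are assumptions. The conclusion that neither reading yields the design figures does not depend on their exact values: it holds for any imperfect correlation.

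This must be settled before results are seen, because it defines what a positive trial means.

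**What to change.** Before any unblinded look, name decline in % predicted FVC, in one pre-specified position, as the single primary outcome, which matches section 1.5. Make MIP, MEP, PCF, SVC and the other versions of FVC secondary, reported with confidence intervals. Use the same primary outcome in the abstract, Introduction, Outcomes and Discussion, and in the registry entry.

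The cost is wording and a registry update; no extra participants are needed for this point. The downside is that four outcomes lose primary status.

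If the sponsor prefers to keep all five, state that success on any one suffices, fix one version of each (position for FVC; position and scale for SVC), apply Holm across the five, and replace the power statement. At the implied effect size, power per outcome at the 0.01 step is about 56–59% with 16 per arm, and about 24 evaluable per arm would restore 80%. Choosing a single primary rather than Holm is a design preference. Leaving the rule unstated is not acceptable.
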